## Abstract

**Background:**

The number of people with diabetes is growing rapidly. Diabetes can cause nerve damage leading to severe pain in the feet, legs and hands, which is known as diabetic peripheral neuropathic pain (DPNP). In the UK, the National Institute for Health and Care Excellence (NICE) recommends amitriptyline, duloxetine, pregabalin or gabapentin as initial treatment for DPNP. If this is not effective, adding one of the other drugs in combination with the first is recommended. NICE points out that these recommendations are not based on robust evidence. The OPTION-DM randomised controlled trial has been designed to address this evidence deficit, with the aims of determining the most clinically beneficial, cost-effective and tolerated treatment pathway for patients with DPNP.

**Methods/design:**

A multicentre, double-blind, centre-stratified, multi-period crossover study with equal allocation to sequences (1:1:1:1:1:1) of treatment pathways. Three hundred and ninety-two participants will be recruited from secondary care DPNP centres in the UK. There are three treatment pathways: amitriptyline supplemented with pregabalin, pregabalin supplemented with amitriptyline and duloxetine supplemented with pregabalin. All participants will receive all three pathways and randomisation will determine the order in which they are received. The primary outcome is the difference between 7-day average 24-h pain scores on an 11-point NRS scale measured during the final follow-up week of the treatment pathway. Secondary outcomes for efficacy, cost-effectiveness, safety, patient-perceived tolerability and subgroup analysis will be measured at week 6 and week 16 of each pathway.

**Discussion:**

The study includes direct comparisons of the mainstay treatment for DPNP. This novel study is designed to examine treatment pathways and capture clinically relevant outcomes which will make the results generalisable to current clinical practice. The study will also provide information on health economic outcomes and will include a subgroup study to provide information on whether patient phenotypes predict response to treatment.

**Trial registration:**

ISRCTN17545443. Registered on 12 September 2016.

**Electronic supplementary material:**

The online version of this article (10.1186/s13063-018-2959-y) contains supplementary material, which is available to authorized users.

## Background

In August 2015, Diabetes UK announced that the prevalence of diabetes had increased by 60% over the previous decade to 3.3 million. Diabetic peripheral neuropathic pain (DPNP) is a serious complication affecting up to 20–26% of these patients [1, 2]. With the prevalence of diabetes set to increase by epidemic proportions over the next decade, DPNP will pose a major treatment challenge [3, 4]. With advanced disease the pain can extend above the feet and may involve the whole of the legs, and when this is the case there is often upper limb involvement also. Moderate-to-severe unremitting lower limb pain is present in over 70% of sufferers [2, 5] and causes insomnia, poor Quality of Life (QoL), unemployment and depression [6–9].

The mainstay of treatment for DPNP is pharmacotherapy. Recent National Institute for Health and Care Excellence (NICE) guidance (173) [10] recommends a choice of amitriptyline, duloxetine, pregabalin or gabapentin as initial treatment. All are licensed treatments for DPNP except amitriptyline, which has been used off-license for more than 25 years. There is moderate evidence for the efficacy of each drug based on Cochrane reviews [11–14] and meta-analyses [15–17], but the best we can hope for any monotherapy is 50% pain relief in 50% of patients [10]. This is often accompanied by side effects (dry mouth, constipation, sedation, dizziness, falls, nausea, oedema, etc.) in around 10–20% depending on dose. NICE recommends combination treatment if initial treatment is not effective (the majority) [10]. However, as NICE points out recommendations are not based on robust evidence as: (1) there are few well-designed head-to-head studies comparing the first-line drugs and their combinations; (2) most studies were flawed with inadequate power, inappropriate endpoints, short duration of follow-up and (3) many randomised controlled trials (RCTs) lacked appropriate health-related QoL (HRQL) measures including functionality and failed to measure impact of drug-related adverse effects on health economics and QoL [10]. An RCT is needed to address these deficiencies.

The aims of the OPTION-DM study will be to determine the most clinically beneficial, cost-effective and tolerated treatment pathway for patients with DPNP. The study has been designed to have direct clinical applicability in the management of DPNP following completion.

### Study objectives

To evaluate if at least one of the three pathways is superior to the other pathways in terms of pain symptoms, quality of life and cost-effectivenessTo evaluate if at least one monotherapy is superior to a different monotherapy in improving pain symptomsTo describe Adverse Event and Serious Adverse Event data for the different treatment pathways for DPNPTo conduct an exploratory analysis to investigate whether there are patient phenotypes that predict response to treatment

## Methods/design

### Study design

OPTION-DM is a multicentre, double-blind, centre-stratified, multi-period crossover study with equal allocation to sequences (1:1:1:1:1:1) of treatment pathways. Three hundred and ninety-two participants will be recruited from secondary care DPNP centres in the UK. A list of participating centres can be found at the end of this paper. Recruitment is expected to take place over 12 months beginning in October 2017. Follow-up will continue for another 12 months.

The study contains an internal pilot with stop-go criteria to assess its feasibility. The recruitment and retention will be reviewed in relation to targets agreed with the funder after 6 months of recruitment. If met, an assessment of attrition to the trial is scheduled after 12 months of recruitment.

The study protocol was written in accordance with the Standard Protocol Items: Recommendations for Interventional Trials (SPIRIT) guidelines (see Additional file 1: SPIRIT Checklist).

### Participants

A number of approaches will be used to identify potential participants: hospital database searches will be completed at each of the study centres; potential patients may be identified during routine hospital appointments at a study centre; the general practitioner (GP) patient registers at around 80 GP surgeries aligned to the study centres will be checked for patients with a diagnosis of diabetes and prescriptions for neuropathic pain medications; Participant Identification Centres (PIC) will be utilised; community podiatry services will be engaged to encourage referrals of potential patients, if applicable; details of the study will be advertised through the use of posters and leaflets in various clinics (for example, diabetes outpatient clinics or GP surgeries); the study will be advertised in a number of locations, such as on charity websites, in local libraries, local newspapers and via local radio stations to inform potential participants about the study.

Potentially eligible participants will be provided with the participant information sheet. Informed consent will be obtained by a medically qualified site investigator trained in Good Clinical Practice.

### Eligibility criteria

#### Inclusion criteria

Participant aged ≥ 18 yearsNeuropathic pain affecting both feet and / or hands for at least 3 months or taking pain medication for neuropathic pain for at least 3 monthsBilateral distal symmetrical neuropathic pain confirmed by the Douleur Neuropathique 4 (DN4) questionnaire at the screening visit [18]Bilateral distal symmetrical polyneuropathy confirmed by a modified Toronto Clinical Neuropathy Score (mTCNS) > 5 at the screening visit [19]Stable glycaemic control (HbA1c < 108 mmol/mol)Participants will have a mean total pain intensity of at least 4 on an 11-point numeric rating scale (NRS; with 0 being ‘no pain’ and 10 ‘worst pain imaginable’) during 1 week off pain medications (baseline period)Willing and able to comply with all the study requirements and be available for the duration of the study. This will be a 1-year study in which all participants will undergo all treatment pathways regardless of treatment response and this point will be made clearWilling to discontinue current neuropathic-pain-relieving medicationsInformed consent form for study participation signed by participant

#### Exclusion criteria

Non-diabetic symmetrical polyneuropathiesHistory of alcohol/substance abuse which would, in the opinion of the investigator, impair their ability to take part in the studyHistory of severe psychiatric illnesses which would, in the opinion of the investigator, impair their ability to take part in the studyHistory of epilepsyContraindications to study medicationsPregnancy/breast feeding or planning pregnancy during the course of the studyUse of prohibited concomitant treatment that could not be discontinuedUse of high-dose morphine equivalent (> 100 mg/day)Liver disease (AST/ALT > 2 times upper limit of normal)Significant renal impairment (estimated glomerular filtration rate (eGFR) < 30 ml/min/1.73m^2^)Heart failure New York Heart Association (NYHA) ≥ class IIClinically significant cardiac arrhythmias on 12-lead ECG or current history of arrhythmiaPatients with a recent myocardial infarction (< 6 months prior to randomisation)Postural hypotension (reduction of > 20 mmHg)Prostatic hypertrophy or urinary retention to an extent which would, in the opinion of the investigator, be a contraindication to the study medicationPatients with other painful medical conditions where the intensity of the pain is significantly more severe than their diabetic peripheral neuropathic pain (patients will not be excluded if the pain is transient in nature)Any suicide risk as judged by the investigator or as defined by a score of ≥ 2 on the suicide risk questionnaireSignificant language barriers which are likely to affect the participant's understanding of the medication schedule or ability to complete outcome questionnairesConcurrent participation in another clinical trial of an investigational medicinal productMajor amputations of the lower limbsActive diabetic foot ulcers

### Washout and baseline period

After providing consent, participants will be instructed on how to washout neuropathic pain medication. The dose will be tapered for 3 days with complete washout for 1–4 days at the investigator's discretion. If the participant is on combination therapy then all drugs will be tapered at once. For participants taking 50-100-mg morphine equivalent the dose will be tapered over a period of up to 2 weeks.

Following the initial washout period, participants will enter the baseline period for 1 week. No neuropathic pain medication is permitted during this week with the exception of paracetamol. From the daily pain scores collected during the baseline period, a mean for the week will be determined and used in subsequent analysis.

### Interventions

#### Treatment pathways

The OPTION-DM will study three treatment pathways:Amitriptyline supplemented with pregabalin (A-P Pathway)Duloxetine supplemented with pregabalin (D-P Pathway)Pregabalin supplemented with amitriptyline (P-A Pathway)

#### Randomisation

Participants will be centrally randomised in the study by the study team at site using the Clinical Trials Research Unit (CTRU) online randomisation system. All participants will receive all three treatment pathways (Table 1). Randomisation will determine the order in which they receive the treatment pathways. Participants will be assigned to one of the six sequences based on a predetermined randomisation schedule stratified by study site using permuted blocks.

**Table 1 Tab1:** Treatment sequences (A = amitriptyline, P = pregabalin, D = duloxetine)

	Treatment pathway 1	Treatment pathway 2	Treatment pathway 3
Sequence 1	A-P	D-P	P-A
Sequence 2	A-P	P-A	D-P
Sequence 3	D-P	A-P	P-A
Sequence 4	D-P	P-A	A-P
Sequence 5	P-A	A-P	D-P
Sequence 6	P-A	D-P	A-P

#### Treatment phases

Each treatment pathway has two treatment phases (Fig. 1). During the first treatment phase, participants will receive monotherapy with the first-line treatment in the pathway. This will last for a total of 6 weeks, including the dose-titration phase.

**Fig. 1 Fig1:**
[figure not shown]
Participant flow

At the week-6 follow-up visit a decision will be taken to either continue on monotherapy or to add second-line treatment as combination therapy based on the 7-day average 24-h pain NRS score during the week preceding the study visit. Participants will be divided into ‘responders’ (pain score ≤ 3) and ‘non-responders’ (pain score > 3) and this will be used to guide treatment during the second treatment phase.

The second treatment phase will last for a total of 10 weeks. Non-responders will commence combination therapy with the addition of second-line treatment for 10 weeks, including the dose-titration phase. Responders will continue on monotherapy for the remainder of treatment phase 2, but this decision may be reversed up to week 13 in the event that a participant becomes a ‘non-responder’ later in the second treatment phase. The dose titration will follow the same schedule.

At the week-16 follow-up visit, participants will be advised to taper-down study medication (3 days) and stop the medication completely (4 days) before commencing the next treatment pathway. The taper dose will be one dose level below the maximum tolerated dose. Participants on dose level 1 will not require a taper dose and will stop study medication completely for 7 days. The first and second treatment phases will be repeated until the participant completes all three pathways.

#### Dose titration

There will be three dose levels for each drug and participants will always start on the lowest dose level of each drug. The schedule of dose escalation will be identical in each treatment pathway, see Fig. 2a and b. Patients with renal insufficiency will receive a modified dosing schedule: eGFR will be measured at screening and at week 16 of each pathway and patients whose eGFR was 30–59 ml/min at their most recent test will receive a lower dose of pregabalin. Pharmacy will be informed of the latest eGFR result with each prescription in order to ensure that the correct dose of pregabalin is dispensed.

**Fig. 2 Fig2:**
[figure not shown]
**a** Dosing and titration schedule for each treatment pathway (*standard pregabalin dosing, estimated glomerular filtration rate (eGFR) ≥ 60 ml/min*). *Participants continue on the maintenance dose of drug from the first treatment phase for the duration of the second treatment phase. **b** Dosing and titration schedule for each treatment pathway (*reduced pregabalin dosing, eGFR 30–59 ml/min*). *Participants continue on the maintenance dose of drug from the first treatment phase for the duration of the second treatment phase

During the first 2 weeks of each treatment phase, the dose will be escalated towards the maximum tolerated dose or maximum permitted dose, whichever is first, based on treatment response (based on the 24-h pain NRS score) and side effect profile.

During the weekly telephone calls and scheduled study visits, the research nurse will evaluate response to treatment and adverse effects to guide dose titration accordingly. If patients are receiving adequate pain relief (24-h pain NRS score ≤ 3) at dose level 1 or 2 then the dose will not be increased further. Patients will also be asked to rate any reported side effects. These will be graded (mild, moderate or severe) and whether side effects are tolerable or intolerable. Any severe or intolerable side effects will require a medication review (i.e. consider dose reduction or discontinuation).

#### Switching treatment during a pathway

At the week-6 visit if there was no change in pain scores from the pre-treatment pathway (baseline), participants will switch to the second-line treatment in the treatment pathway.

If there is significant intolerance to first-line treatment; for example, due to side effects which are severe or which the patient describes as intolerable, participants can switch to the second-line treatment in the treatment pathway as a monotherapy. In this situation the switch can be made immediately, at any time, without the need to washout the first-line treatment. The second-line treatment will be continued as a monotherapy for the remainder of the treatment pathway; i.e. up to the week-16 visit. If there is significant intolerance to the second-line treatment in the pathway, the participant will stop the study treatment but will remain in the study for follow-up.

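### The article gives two conflicting mandatory week-6 instructions for a participant whose pain is unchanged and above 3: add the second-line drug, or switch to it

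*Protocol article*

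**What the plan says.** All references are to the protocol article.

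- *Treatment phases* (text after Fig. 1), options at week 6: "a decision will be taken to either continue on monotherapy or to add second-line treatment as combination therapy". Switching is not among them. The decision uses the 7-day average 24-hour NRS score.
- Same section, the split: "Participants will be divided into ‘responders’ (pain score ≤ 3) and ‘non-responders’ (pain score > 3").
- Same section, the consequence: "Non-responders will commence combination therapy with the addition of second-line treatment for 10 weeks, including the dose-titration phase". No exception is stated.
- *Dose titration*, note to Fig. 2: "Participants continue on the maintenance dose of drug from the first treatment phase for the duration of the second treatment phase".
- *Switching treatment during a pathway*, opening sentence: "At the week-6 visit if there was no change in pain scores from the pre-treatment pathway (baseline), participants will switch to the second-line treatment". The following paragraph gives a separate switch rule for intolerance.
- *Washout and baseline period* defines one baseline week, off neuropathic pain drugs, after the initial washout: "From the daily pain scores collected during the baseline period, a mean for the week will be determined and used in subsequent analysis".
- *Treatment phases*, on the gap after each pathway: "participants will be advised to taper-down study medication (3 days) and stop the medication completely (4 days) before commencing the next treatment pathway". Participants on dose level 1 have no taper and stop for the full 7 days.

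**The concern.** Two sentences, both phrased as what will happen, apply to the same person at the same visit and lead to different regimens. One keeps the first-line drug and adds the second. The other replaces the first with the second, taking switch in its ordinary sense. Neither refers to the other or says which prevails.

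The primary outcome is the 7-day average pain in week 16. The week-6 decision governs the 10 weeks before that point (6 + 10 = 16), so it settles what is being taken when the primary outcome is measured. If sites read the text differently, a pathway label would stand for different treatment rules at different sites, and the pathway contrast would lose a single meaning. The trial aims to inform practice about whole pathways, so the pathway rule is part of what is being tested.

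**Working it through.** The article gives no figure on this point, and the sample size (294 evaluable, 392 randomised) does not depend on it. The check is a comparison of the rules.

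**Inputs.** Entry: baseline mean of at least 4 (*Inclusion criteria*). Responder cut-off: 3 (*Treatment phases*). Gap between pathways: 3 taper days plus 4 days off, or 7 days off at dose level 1 (*Treatment phases*).

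**Step 1: do the rules overlap?** Let B be the mean in the pre-randomisation baseline week and W the week-6 mean. Entry requires B ≥ 4. If pain is unchanged, W = B ≥ 4 > 3. Against that baseline, every unchanged participant is therefore a non-responder and meets both instructions.

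| Week-6 result against B | *Treatment phases* | *Switching* section |
|---|---|---|
| Improved, W ≤ 3 | continue | silent |
| Improved, W > 3 | add | silent |
| Exactly unchanged, W = B | add | switch |
| Worsened, W > B | add | silent if read literally |

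**Step 2: what does no change cover?** If daily scores are whole numbers and all seven are recorded, a 7-day mean moves in steps of 1/7 = 0.14. Exact equality is then a narrow event. Read literally, an exactly unchanged participant loses the first-line drug, while a worsened one keeps it and gains the second. The text does not say whether worsening, or a trivial improvement, counts as no change.

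**Step 3: unchanged from what?** The switching section refers to a baseline before the treatment pathway. There are two readings.

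- The single pre-randomisation week. Step 1 then applies in all three pathways.
- The 7 days before each pathway. Before pathways 2 and 3, participants above dose level 1 spend 3/7 = 43% of those days on a taper dose, and those on dose level 1 spend 0/7. The minimum of 4 is an entry condition for the pre-randomisation week only, so a pathway-specific reference could be 3 or less. An unchanged participant would then be a responder who continues under one section and must switch under the other.

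To show that the readings can differ, suppose that pain is 6 off drug and 4 on drug, with taper days at the on-drug level. The pre-pathway mean is (3 × 4 + 4 × 6)/7 = 36/7 = 5.14, against 6 off drug. A week-6 score of 6 would be unchanged on one reading and worse on the other. These pain levels are assumed.

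**Step 4: what follows for week 16?** For an unchanged participant (A = amitriptyline, D = duloxetine, P = pregabalin):

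| Pathway | If the second drug is added | If switched |
|---|---|---|
| A-P | A + P | P |
| D-P | D + P | P |
| P-A | P + A | A |

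For someone unchanged on both amitriptyline and duloxetine, the A-P versus D-P comparison sets two different combinations against each other on one reading, and pregabalin alone in both on the other. The reading thus changes what the contrast compares. It does not by itself show that either pathway gains.

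**The case against.** The strongest answer is that the article sets out a general rule and an exception under its own heading. The Discussion supports this. *Why examine treatment pathways?* expects patients whose monotherapy does nothing to be moved to another agent, and *Efficient design with 16-week treatment pathways* ties the combination phase to partial benefit. Together these suggest a three-way scheme: enough relief, continue; partial benefit, add; no benefit, switch. The responder split is also described as guiding treatment. The Fig. 2 note is weak evidence to the contrary, because the figure is not shown and the note may describe only the add-on schedule. The full protocol (version 7.0), which the article condenses, may define no change numerically.

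Much of this stands. The exception is the likelier intention, and a missing threshold alone would not be a finding in a journal article. But the treatment-phase text lists two options and carves nothing out for the third. Nor does the three-way scheme fit the literal wording: a worsened participant has no partial benefit, yet falls under the combination rule. A statistical analysis plan could not repair this either, because the choice is made at the site during treatment.

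It is also fair that every participant receives all three pathways, that randomisation is stratified by site and that the treating physician does not know the drug. A site's reading would therefore tend to apply to all three pathways alike. That argues against a demonstrated bias. It does not make the intervention uniformly defined.

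**Conclusion.** The conflict is real and stands in the printed text: unchanged pain above 3 at week 6 attracts two mandatory and different instructions. Against the pre-randomisation baseline the overlap is complete, from the entry criterion alone. No change and its reference period are open to more than one reading. The consequence is an inconsistently defined intervention if sites differ. Whether they did is not known from the article.

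The size cannot be computed. The article gives neither the expected change from baseline nor its spread. The within-patient SD of 1.65 belongs to the comparison of two active treatments, so any percentage would rest on invented inputs. The article itself expects only a very small minority either to stay on monotherapy or to be switched.

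Three stronger conclusions are tempting and are not supported:

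- **That the reference in pathways 2 and 3 is contaminated by the previous treatment.** No section says that a fresh reference is taken. If the pre-randomisation week is meant, the issue disappears, and participants on dose level 1 have 7 drug-free days in any case.
- **That the most effective pathway is favoured.** This needs the pathway-specific reading. The primary outcome is the week-16 score itself, not a change, and the stated model has no baseline term. No direction of bias between pathways is shown.
- **That the 30% and 50% success outcomes lack a baseline.** The article defines one baseline week and says that its mean is used in later analysis. Further detail belongs to the analysis plan.

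This is a clarification worth making, not a challenge to the primary analysis or the sample size.

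**What to change.** Reconcile *Treatment phases* and *Switching treatment during a pathway* into one week-6 rule whose categories are mutually exclusive and cover every result. The investigators should define no change on the 7-day mean, say how worsening is handled, and name the reference period for pathways 2 and 3. Which action each category receives is a clinical decision for them. If the full protocol already settles these points, the article and site instructions should be checked against it.

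The cost is a clarifying amendment and a site memo. No sample-size figure or analysis model changes. Because recruitment had already begun, a tabulation of week-6 actions (continue, add, switch) by pathway and site would show how far readings differed before the clarification.
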